#### Secondary outcome

3.8.2

The secondary outcome assessment measures the change from the baseline in the numerical rating scale (NRS). The time frame is as follows: screening, baseline, and days 5, 11, 21, 28, and 84. The NRS range is 0 to 10, with 0 being no pain and 10 being the worst pain possible. In addition, the following outcome assessments are surveyed as a secondary outcome measurement: Change from the baseline in a physical condition related to mobility, which is a 5-m walking test at a comfortable speed of −5 mWT (meters/second) at every visit (time frame: screening, days 11 and 84); change from the baseline in a physical condition related to endurance, which is a sit-to-stand test (seconds) at every visit (time frame: screening, days 11, 84); change from the baseline in the timed up and go test, which is a functional test for evaluating the time to rise from a chair, walk 3 m, turn around, walk back to a chair and sit down (abnormal cutoff value >12 s) at every visit (time frame: screening, day 11, day 84); change from the baseline in the alternative step test, which is a functional test measuring the clinical balance performance, and it has been shown to predict fall risk among elderly subjects (seconds) at every visit (time frame: screening, day 11, day 84); and change from the baseline in the range of motion test, which compares the flexion and extension angle using a long-arm goniometer between the experimental and comparator groups (time frame: screening, baseline, days 5, 11, 28, and 84).

#### Safety and adverse events monitoring

3.8.3

The safety assessment includes

1.adverse reactions,2.vital signs, and3.clinical laboratory testing.

The subinvestigator will record the details of any adverse reactions and the use of concomitant medications during the clinical trial in the case report form. In case of an adverse reaction, the symptoms and signs of the adverse reaction, duration (start date/end date), severity, result, significance, causal relationship to the drug under clinical investigation, and measures taken for its alleviation will be recorded. The names, dosages, duration of administration, reason for administration, etc, of the concomitant medications will be recorded in detail.

Clinical laboratory tests will be performed at screening, V5, V9, FU2, and FU3. Since this study will evaluate the safety of the usual care and acupuncture combination, it differs from clinical studies that evaluate the safety and pharmacokinetic properties of drugs. Therefore, this study conducts clinical laboratory tests for the following items for the purpose of the standard safety lab test:

1.hematology: hemoglobin, hematocrit, red blood cell count, white blood cell count, and differential count, platelet count;2.serum chemistry: glucose fasting, aspartate aminotransferase (AST), alanine aminotransferase (ALT), blood urea nitrogen (BUN), electrolytes (sodium, potassium, and chloride), serum creatinine (SCr), erythrocyte sedimentation rate (ESR), C-reactive protein (CRP); and3.coagulation: D-dimer, fibrin degradation products (FDP);4.γ-glutamyl transpeptidase (γ-GTP), alkaline phosphatase, creatinine phosphokinase (CPK), uric acid, total bilirubin, total protein, albumin, osteocalcin, carboxy-terminal collagen crosslinks (CTX), urine analysis: pH, protein (albumin), glucose, leukocyte esterase, and blood were performed only at screening.

#### Early termination or dropout

3.8.4

The early termination or dropout criteria are as follows:

1.Violation of the inclusion/exclusion criteria2.Withdrawal of consent for participation3.Adverse reactions (including serious adverse reactions)

Adverse reactions refer to undesirable and unintended signs, symptoms, or diseases and do not necessarily have a causal relationship with the interventions administered during a clinical trial. However, since the present clinical trial involves patients who underwent TKR, adverse reactions may be deemed symptoms or side effects caused by TKR at the discretion of the operating surgeon and principal investigator. Symptoms that the principal investigator deems as unassociated with the intervention of this clinical trial are not classified as adverse reactions that occur during this clinical trial.

4.Poor compliance (compliance below 70% in the final compliance assessment) or inability to comply5.Violation of the clinical trial protocol6.Other reasons deemed valid by the researchers7.Diagnosis of an infection in the recovery room

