## Introduction

1

Total knee replacement (TKR) is a surgical procedure that is being increasingly performed due to population aging and increased life expectancy in South Korea. The number of TKR procedures increased by over 135%, from 45,879 in 2015 to 62,344 in 2019. The medical cost of public health insurance associated with TKRs totaled 37,077,059,000 won (∼32,638,256 US dollars) in 2015 and increased to 55,499,427,000 won (∼48,850,829 US dollars) in 2019.^[1]^ The age distribution of patients undergoing TKR shows that 36.2% of the patients were aged 60 to 69 years, 48.6% were aged 70 to 79 years, and 8.7% were aged ≥80 years,^[2]^ indicating that TKR is primarily performed on elderly patients. A large number of patients undergo TKR due to degenerative knee arthritis. Consistent with the high incidence of TKR in South Korea, the number of patients seeking acupuncture for pain management and enhancement for rehabilitative therapy effects and bodily function not only before but also after TKR has also been increasing.

In the western-medicine-based clinical settings in South Korea, acupuncture treatment after TKR is considered unsafe regardless of the acupuncture points in use because of the risk of infection and reoperation, and the practice is often rejected or prohibited. Furthermore, according to a recent systematic review, including acupuncture in a rehabilitation program is beneficial as an adjunct to opioids for pain management across several types of postsurgical conditions.^[3]^ However, the results of studies investigating the effect of acupuncture after TKR are not in concordance.^[4–7]^ Moreover, no previous study has examined the efficacy, safety, and cost-effectiveness of post-TKR acupuncture rather than focusing solely on its efficacy.

Therefore, it is worth assessing the effectiveness, safety, and cost-effectiveness of acupuncture as an adjunctive therapy in patients following TKR in a pilot study.

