##### Safety variables

3.9.3.3

The number of adverse reactions (vital signs, abnormal values in a physical test, acute reactions observed after vaccination, and local or systemic reactions) will be determined for each group, and their incidence and 95% confidence intervals will be presented. The chi-square test will be used for intergroup comparisons of adverse reactions.

Continuous data such as blood or blood chemistry test parameters, physical test parameters, and vital signs will be presented for each group and assessed using descriptive statistics. A paired *t* test will be used for comparisons before and after the treatment, and Student's *t* test will be used for intergroup comparisons. The frequency and percentage will be presented for categorical data such as urine test results, and McNemar's test will be used to determine normal and abnormal conditions for each visit.

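### The adverse-reaction definition contradicts itself, so the between-arm safety comparison can be read as resting on counts already filtered by judged cause

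*Protocol article*

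**What the plan says.** The definition stands in section 3.8.4 of the protocol article, under item 3 of the early-termination and dropout list. It has three steps:

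- Adverse reactions are undesirable and unintended signs, symptoms or diseases that "do not necessarily have a causal relationship with the interventions administered during a clinical trial".
- Because all participants have had a knee replacement, "adverse reactions may be deemed symptoms or side effects caused by TKR at the discretion of the operating surgeon and principal investigator". No criteria for this attribution are given.
- "Symptoms that the principal investigator deems as unassociated with the intervention of this clinical trial are not classified as adverse reactions".

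Section 3.8.3 has the subinvestigator record details of any adverse reaction. Among them, "causal relationship to the drug under clinical investigation, and measures taken for its alleviation will be recorded", although the intervention under study is acupuncture and not a drug.

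Section 3.9.3.3 presents the number of adverse reactions per group with incidence and 95% confidence interval, and adds: "The chi-square test will be used for intergroup comparisons of adverse reactions". Its list of what counts includes "acute reactions observed after vaccination", which does not fit this trial, as well as a general category of local or systemic reactions. It does not name infection or reoperation.

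The Introduction says that, in Korean hospitals practising western medicine, "acupuncture treatment after TKR is considered unsafe regardless of the acupuncture points in use because of the risk of infection and reoperation". Section 2 makes safety part of the hypothesis.

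**The concern.** The first and third steps of the definition cannot both hold. If no causal link is needed, an event is an adverse reaction whatever the principal investigator thinks of its cause. If the third step governs, the event disappears before the arms are compared.

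This matters because the safety question is comparative. A randomised comparison of event counts is protected from bias only if events enter the count by the same rule in both arms. A filter on judged relatedness replaces that rule with an opinion about cause. In this setting the opinion is especially hard to apply: infection and reoperation are complications that can readily be put down to the operation itself, and they are also the events that make acupuncture after knee replacement contentious. A count from which such events can be removed by attribution does not answer the question the Introduction raises. Events never classified as adverse reactions may also be hard to recover later.

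**Working it through.** **The plan's own figure.** The only design figure needed here is the arm size, and it reproduces. From section 3.3: difference 3.60, SDs 4.05 and 4.16, two-sided alpha 0.05, power 80%. Pooled SD = √[(4.05² + 4.16²)/2] = 4.105. The normal approximation gives 21 per arm; the noncentral t calculation gives 22 (power 0.811), as stated. With 10% dropout, 22/0.90 = 24.4, rounded up to 25 per arm. One event is therefore 1/25 = 4 percentage points of an arm's incidence.

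**Does the rule work alike in both arms?** Section 3.8.4 does not define the intervention to which an event must be related. There are two readings.

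- *The intervention is acupuncture.* Controls receive none, so no control event can be associated with it and the control count is empty by construction. The acupuncture-arm count depends on judgement. Acupuncture looks worse than it is.
- *The intervention is the whole package, including usual care.* Events in both arms may count, but each can instead be attributed to the knee replacement, without criteria. The acupuncture arm has one candidate cause more than the control arm. The direction of bias is open.

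Neither reading compares like with like.

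**Is the judgement made without knowledge of the arm?** Section 3.2 calls the trial open-label and assessor-blinded. Section 3.6 says the investigator cannot be blinded, then that the investigator maintains blinding when evaluating participants. It does not state the principal investigator's or the surgeon's status separately. Nothing requires relatedness to be judged without knowledge of allocation.

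**Possible size.** The documents give no event rates and no share of events likely to be excluded, so the values below are assumptions. If a proportion p of patients truly has an event and a share q is excluded, the counted number in an arm is Binomial(25, p(1 − q)). Comparisons use the two-sided Fisher exact test, which section 3.9.1 allows beside the chi-square test.

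*Equal true rates, unequal exclusion (chance of a false significant difference):*

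| Excluded in one arm / the other | Expected counts at p = 20% | p = 20% | p = 30% |
|---|---|---|---|
| 0% / 90% | 25×0.20 = 5.0 v 25×0.20×0.10 = 0.5 | 0.30 | 0.66 |
| 0% / 100% | 5.0 v 0 | 0.38 | 0.81 |
| 50% / 90% | 2.5 v 0.5 | 0.02 | 0.10 |

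The result is the same whichever arm is discounted; only the direction changes. If acupuncture is the intervention and all acupuncture-arm events are retained, the second row applies.

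*Equal exclusion in both arms:* for a true 30% v 4%, power is 0.605 with all events counted, 0.119 with half excluded and 0.003 with 80% excluded. At a true rate of 10%, the chance of at least one counted event in an arm is 1 − (1 − 0.10(1 − q))²⁵. This is 0.93 with all events counted, 0.72 with half excluded, 0.40 with 80% excluded and 0 with all excluded.

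**The case against.** The strongest reply is that the exclusion sentence sits in a list of dropout reasons and may only limit which events lead to withdrawal. Section 3.8.3 records any adverse reaction with a causality field, which would be largely redundant if unrelated events had already been removed, and section 3.9.3.3 does not refer to the filter. This stands in part. A reader might infer that section 3.9.3.3 certainly tests filtered counts; the documents do not establish that. But the sentence is worded generally, for the trial as a whole, and no other definition is offered. The reference to GCP in section 3.8.5 covers only matters the protocol does not specify, and this one it does.

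Other stronger readings are tempting and should not be made:

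- *That every event due to the knee replacement is removed.* The text says only that reactions may be so attributed; exclusion follows from joining two sentences.
- *That those judging know the arm.* This is likely in an open-label trial, but section 3.6 is inconsistent on it.
- *That the plan would hide harm from acupuncture.* A case such as 0% v 12% (0 v 3 of 25) needs assumed counts and attribution in one direction only. Under one reading of the intervention the bias runs the other way.
- *That the dropout criterion "Diagnosis of an infection in the recovery room" conceals infections caused by needling.* Acupuncture starts at Visit 2, on postoperative day 3 ± 2 (Table 1). Taken at face value, such an infection precedes needling.

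Some information is also outside the filter. White cell count, ESR and CRP are measured at V5, V9, FU2 and FU3 and compared between arms. The category of local or systemic reactions in section 3.9.3.3 could include infection. Section 3.9.3.4.4 gives surgical site infection as an example of a treatment-related dropout and keeps such cases in the economic evaluation. These points soften the concern, but a laboratory value does not record a reoperation, and the provision in section 3.9.3.4.4 concerns the economic evaluation.

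Finally, rare events would seldom reach significance at this size even if all were counted: power is about 0.02 for an assumed 10% v 2%. That is right, and it places the main harm in the reported counts and intervals, not in a lost test.

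**Conclusion.** The concern holds as an internal contradiction with a possible, not certain, effect on the safety results. Section 3.8.4 both denies and requires a causal link, and sections 3.8.3 and 3.9.3.3 do not settle which applies. Followed as written, the text allows the adverse-reaction counts to be filtered by judged cause, by a rule that cannot be applied equally in the two arms and with no requirement for masked judgement. Infections and reoperations could be lost or counted unequally.

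The certain part of the size is that each event included or excluded moves an arm's incidence by 4 points. The probabilities of a false difference (0.30 to 0.81 under near-total or total exclusion in one arm only, 0.02 to 0.10 under milder imbalance) rest on assumed true rates of 20% to 30% and assumed excluded shares. They show what the rule permits and do not forecast what will happen. The direction of any bias cannot be told from the documents.

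**What to change.** - Delete the exclusion sentence from section 3.8.4, and state that attributing an event to the knee replacement does not remove it from the adverse-event record. If the sentence was meant only to limit which events count as a reason for dropout, say so there and keep it apart from the definition.
- Record all adverse events through FU3 in both arms and tabulate them by arm regardless of judged cause, with infection and reoperation as explicit lines. The incidence, 95% confidence interval and between-group comparison in section 3.9.3.3 should refer to this table.
- Keep relatedness as a separate, descriptive field. Reword the field in section 3.8.3 so that it refers to the trial intervention and not to a drug, and define that intervention.
- Replace the vaccination wording in section 3.9.3.3 with reactions that can occur in this trial.
- Reconcile sections 3.8.3, 3.8.4 and 3.9.3.3 so that one definition serves all three.

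The cost is a change of wording and one more table. Reported event rates will be higher in both arms, because ordinary postoperative events will be counted. Masked review of relatedness would strengthen the descriptive table but needs people and procedures; the main comparison does not depend on it once all events are counted.

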### Recruitment, randomization, blinding, and nonblinding

3.6

Advertisements for patient recruitment will be posted on the Catholic Kwandong University International St. Mary's Hospital bulletin boards, along with posters, banner advertisements and internet cafes. All advertisements will be run after IRB approval.

Individuals who have given written consent for participating in the study will be assigned a screening number in order of the outpatient visit at screening. Unblinded subinvestigators who do not influence the research results and analysis will refer to the randomization list that has been prepared by a commissioned professional statistician and will assign participation numbers. Participants will be allocated to the usual care group and the usual care plus acupuncture group at a ratio of 1:1. A block randomization table is generated by an independent statistician, and patients are assigned to one of two groups according to the randomization table. The screening numbers, randomization numbers, and initials assigned to each participant are used as subject identification codes to identify the participant until the end of the clinical trial.

The usual care used in this study is not a clinical investigation product and does not require allocation concealment, since it is administered to all the groups. Moreover, it is impossible to blind the investigator and the participant in each group due to the nature of the study intervention, which is based on the contact between the patient and the medical staff. Instead, the investigator maintains blinding to prevent bias in evaluating the participant. If the clinical trial is completed, all clinical report forms (CRFs) are collected, the database process is terminated, and unblinding will be performed if required for statistical analysis.

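### Section 3.8.4 lets events judged unrelated to the intervention fall outside adverse reactions, so surgery-attributed events could be missing from the between-arm safety count

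*Protocol article*

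**What the plan says.** All references are to the protocol article.

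- **Section 3.8.4 (Early termination or dropout), under the third dropout criterion.** Adverse reactions are unwanted signs, symptoms or diseases that "do not necessarily have a causal relationship with the interventions administered during a clinical trial". Because the patients have all had a knee replacement, the text goes on, "adverse reactions may be deemed symptoms or side effects caused by TKR at the discretion of the operating surgeon and principal investigator". It closes: "Symptoms that the principal investigator deems as unassociated with the intervention of this clinical trial are not classified as adverse reactions".
- **Section 3.8.3 (Safety and adverse events monitoring).** The subinvestigator records any adverse reaction on the case report form. Among the details, "causal relationship to the drug under clinical investigation, and measures taken for its alleviation will be recorded".
- **Section 3.9.3.3 (Safety variables).** Adverse reactions are counted per group, under a list of types that includes local and systemic reactions, and "their incidence and 95% confidence intervals will be presented". Then: "The chi-square test will be used for intergroup comparisons of adverse reactions".
- **Sections 1 and 2.** The Introduction gives infection and reoperation as the reason why acupuncture after knee replacement is often refused. The Objective makes safety part of the hypothesis.

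**The concern.** The term that section 3.9.3.3 counts is the term that section 3.8.4 narrows. An event that the principal investigator judges unassociated with the intervention stops being an adverse reaction and, read literally, has no place in the count. After a knee replacement, many events can be put down to the operation, and section 3.8.4 expressly allows that at the discretion of the surgeon and principal investigator, without criteria.

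The events most easily put down to surgery include infection and reoperation, which are the safety question the trial sets itself. If such events are reclassified before they are counted, a low incidence could mean few events or could mean events moved elsewhere, and the adverse reaction table would not show which.

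**Working it through.** **1. The rules side by side**

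| Section | Rule | Does an unrelated event count? |
|---|---|---|
| 3.8.4, definition | No causal link needed | Yes |
| 3.8.4, closing sentence | Judged unassociated, so not an adverse reaction | No |
| 3.8.3 | Any adverse reaction is recorded, with causality as a field | Implied yes: the field would have little use if unrelated events were already removed |
| 3.9.3.3 | List of reaction types with no attribution filter | Not addressed; nothing excludes it |

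The closing sentence of 3.8.4 is the only one that removes an event for lack of association. The article does not say which rule governs the count.

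**2. Does another section settle it?**

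- Section 3.8.5 turns to ICH and Korean GCP only for matters that the protocol does not specify. This matter is specified.
- Section 3.9.3.4.4 names surgical-site infection, but only to keep such dropouts in the economic evaluation and its intention-to-treat analysis.
- Section 3.10 has the contract research organization check that adverse event reports are complete. It does not change what counts as an adverse reaction.
- White cell count, ESR and CRP are measured at screening, V5, V9, FU2 and FU3 (3.8.3) and compared between groups (3.9.3.3). A difference in group means is some signal of infection, but it is not a counted infection or reoperation.

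**3. Weight of one omitted event**

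Input: 25 participants per group (section 3.3), all assumed to be in the denominator. The article does not name an interval method; exact (Clopper-Pearson) limits are used here.

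- One event: 1/25 = 4.0 percentage points.
- For 0/25 the upper limit is 1 − 0.025^(1/25) = 13.7%, and the lower limit is 0.
- For 1/25 the upper limit is the p that solves (1 − p)^25 + 25p(1 − p)^24 = 0.025, which gives 20.4%. The lower limit is 1 − 0.975^(1/25) = 0.1%.
- For 2/25 the same method gives 1.0% to 26.0%.

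If one event occurred in an arm and was reclassified, the reported result would move from 4% (0.1% to 20.4%) to 0% (0% to 13.7%).

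**4. Effect on the test**

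The article gives no event rates, so this is an assumed example: 4/25 against 1/25, fully recorded. Pearson chi-square without correction = 50 × (4×24 − 1×21)² / (5 × 45 × 25 × 25) = 281,250 / 140,625 = 2.0, p = 0.16. Fisher's exact p = 0.35. The comparison is non-significant even with every event counted, so at this size the loss falls mainly on the count and its interval.

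**The case against.** The strongest reply is that the wording is a general definition followed by an exception for this trial. The second sentence opens with a contrast and a reason, so the paragraph can be read without strict contradiction. That stands. The difficulty is that the exception is unwise and does not fit 3.8.3 and 3.9.3.3.

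A second reply is placement: the text explains which events end participation, while safety recording belongs to 3.8.3. This makes the harm conditional but does not remove it. The closing sentence speaks of reactions during the trial in general, and 3.8.3 and 3.9.3.3 use the same term without redefining it. The list in 3.9.3.3 could well take in a wound infection, but it describes types of event and does not say how attribution is handled.

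Three stronger readings are tempting and are not supported:

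- *Surgical-site infections will be excluded.* Nothing says so. Section 3.9.3.4.4 gives them as an example of dropout linked to the target disease or the trial treatment, which suggests that the authors did not regard them as unassociated. Exclusion is a possibility that the rule leaves open.
- *The intervention is undefined.* Section 3.4 sets out usual care and acupuncture under that heading, and 3.8.3 says the trial evaluates the two in combination.
- *The exclusion works unequally between arms because attribution is unblinded.* Section 3.6 says both "it is impossible to blind the investigator and the participant in each group due to the nature of the study intervention" and "Instead, the investigator maintains blinding to prevent bias in evaluating the participant". The article does not say whether attribution is made blind, and a condensed article may leave that to the full protocol. Neither a difference between arms nor its direction can be derived.

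**Conclusion.** The concern holds in a limited form. Section 3.8.4 contains a stated rule that, if followed, could leave events attributed to the operation out of the incidence, confidence interval and chi-square comparison in 3.9.3.3. The rule sits badly with the causality field and the unfiltered list elsewhere, and no other section cancels it.

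The size of any effect is unknown, since it depends on event rates and attribution habits that the article does not give. What can be said, assuming 25 per arm and exact limits, is that each omitted event takes 4 points off an arm's incidence, and that losing a sole event lowers the upper limit from 20.4% to 13.7%. The significance test would often be unaffected. The sponsor should correct this: safety is part of the hypothesis, and in a trial of this size the descriptive count and its interval carry most of the safety message.

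**What to change.** 1. Delete the closing sentence of the adverse reaction paragraph in 3.8.4 and keep the opening definition.
2. State in 3.9.3.3 that all adverse events are counted in both arms from V2 to FU3 whatever their attributed cause, and name surgical-site or joint infection and reoperation among them.
3. Record attribution, including attribution to surgery, only in the causality field of 3.8.3, and reword that field for acupuncture in place of an investigational drug.
4. Report events judged related as a subset of all events, by arm.

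The cost is wording only. Table 1 already schedules adverse reaction assessments at V2 to V10 and FU1 to FU3 (9 + 3 = 12), so no visit or test is added. The small downside is a longer list of plainly surgical events in both arms.
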